## 15. FURTHER CONSIDERATIONS ON THE ANALYTICAL APPROACH

### 15.1 Missing data

Missing data will be checked and either corrected if wrong or left if legitimate. Missing data will not be imputed (but see sensitivity analysis). The amount of missing data will be quantified and analyses for variables with missing data will be noted as such.

Mixed effects models usually do not require imputation as they are usually robust to missing data (although this depends if missing data is missing at random or not).

### 15.2 Outliers

Outliers will be checked and either corrected if wrong or left if legitimate. Outliers will not be removed. Analyses for variables with outliers will be noted as such. There are various methods of identifying an outlier, including the “3SD’s beyond the mean” heuristic. We will use the “1.5IQR rule”: outliers will be those points below  $Q1 - 1.5IQR$ , or above  $Q3 + 1.5IQR$  [6].

### 15.3 Subgroup Analyses

As stated in the section named “Statistics and Analysis” in the protocol, no formal subgroup analyses are planned. However, subgroup analyses requested after the protocol was written are permissible on an exploratory and descriptive basis at the discretion of the Trial Statistician. These subgroup analyses are referred to as “informal”. With the exception of the stratification factors (see sensitivity analysis below) those informal analyses are descriptive and without the need to calculate or report p-values.

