## 4. STATISTICAL PRINCIPLES

### 4.1 Statistical Significance and Multiple Testing

*See also the protocol section “The Level of Statistical Significance”*

P-values will not be reported given the feasibility nature of the trial. There will be no adjustment for multiple testing. The 95% confidence intervals will be presented but regarded as nominal and descriptive.

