#### 6.5 Pre-specified Subgroup Analysis

*See also the protocol section "Description of the Statistical Methods"*

No subgroup analyses are planned.

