### 4.2 Output variables

We expect to model all secondary outcome variables, except survival, recurrence, new primary/secondary cancer, re-admission rates, re-operation rates, costs and resource use, and adverse events. The final decision will depend on the available data. For example, if the counts for conversion to open surgery rates are very low, we will not model this outcome.

Therefore, we plan on analysing:

- Morbidity (five variables not including 2iii survival)
- Operative outcomes (seven variables not including re-operation and re-admission rates)
- Hospital stay (two variables)
- Anthropometry (two variables)
- Fitness (one variable)
- Health-related quality of life (HRQoL) (three variables)

That's twenty variables equating to at least 20 models, as some of those variables will be further subdivided (eg HRQoL variable "EQ-5D-5L" has two subdivisions, index and VAS).

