### 12.4 xxiii. EORTC-QLQ-CR29

This secondary outcome is displayed by timepoint. The information to calculate it is derived from the CRF EORTC QLQ - CR29. It is a continuous variable and a score. The scoring rules are in the appendices. The score will be calculated for the 29 individual items. The 29 individual items will be descriptive only

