## 15.4 Sensitivity Analyses

Sensitivity analyses will be done on at least the following:

- **Per-protocol analysis.** The per-protocol analysis will repeat the above models using the per protocol population as defined in section 3.
- **Stratification factors.** The two stratification factors are performance status (“0” vs “1-2”) and age at diagnosis (“< 70 years” and “ $\geq$ 70 years”). For sensitivity analysis we will do the following:
  - Repeat the models with an interaction term between age at diagnosis (“< 70 years” and “ $\geq$ 70 years”) and treatment. This will be expanded to “...and treatment and time” if time is an input variable, see below.
  - Repeat the models with an interaction term between performance status (“0” vs “1-2”) and treatment. This will be expanded to “...and treatment and time” if time is an input variable, see below.
  - Models measuring the state at one timepoint (eg discharge) or the state change between two timepoints will not need a time variable. Models measuring the state at two or more timepoints (eg baseline vs admission vs 30-days post-op) will need a time variable. In such cases, the interaction above will include the time variable. The paper at [7] is an example of this.
- **Other.** Other sensitivity analyses may be conducted if deemed necessary by the Trial Statistician.

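### The secondary-outcomes supplement excepts the age and performance-status interactions from the trial's descriptive, no-p-value rule, contradicting the protocol and SAP without saying whether p-values will be reported

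*Combined protocol and SAP*

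**What the plan says.** **Parent documents.** SAP 4.1 states: "P-values will not be reported given the feasibility nature of the trial". It adds that there is no multiplicity adjustment and that the 95% confidence intervals are nominal and descriptive. Protocol 11.7 says the same. SAP 6.5 states "No subgroup analyses are planned", as does protocol 11.2. SAP 6.4 plans no sensitivity analyses and leaves room for them only if the data depart from expectation.

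**Supplement on secondary outcomes.** Section 15.3 repeats that no formal subgroup analyses are planned. It allows later ones on an exploratory, informal footing and then says that, with the "exception of the stratification factors (see sensitivity analysis below) those informal analyses are descriptive and without the need to calculate or report p-values". Section 15.4, under the sensitivity heading, gives two instructions: "Repeat the models with an interaction term between age at diagnosis" and treatment, and "Repeat the models with an interaction term between performance status" and treatment. Both become three-way interactions with time when an outcome is measured at two or more timepoints.

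**Scale.** Supplement 4.2 totals the outcomes to be modelled: "That's twenty variables equating to at least 20 models". The same section qualifies this: "The final decision will depend on the available data".

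**Reading the coefficients.** Supplement 4.1 says that in any model containing an interaction, the interaction term is taken as the treatment effect.

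**The concern.** A treatment-by-baseline-factor interaction asks whether the effect differs between subgroups. It does not ask whether the main result is robust to an assumption, so the sensitivity label does not fit.

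The exception in 15.3 has content only if these analyses are not confined to description, or if p-values are contemplated for them. The parent documents make no such exception. The case for leaving multiplicity unadjusted is that nothing is formally tested. If p-values were attached to two interactions in every secondary model, that case would no longer cover them.

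Two analysts could follow the documents in good faith and produce different outputs, one with interaction p-values and one without. That should be settled before results are seen. The rule in supplement 4.1 adds a second ambiguity: applied literally to the 15.4 models, it would report effect modification by age or performance status as the treatment effect.

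**Working it through.** **1. The plan's own count.** Supplement 4.2 lists 5 morbidity, 7 operative, 2 hospital-stay, 2 anthropometry, 1 fitness and 3 quality-of-life variables: 5 + 7 + 2 + 2 + 1 + 3 = 20. This reproduces the stated figure. Two factors × 20 models = 40 interaction terms.

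**2. How firm is 40?** It is a planned count and not a minimum.
- Downward: low-count outcomes may be dropped. EORTC-QLQ-CR29 is among the 20, yet supplement 12.4 says "The 29 individual items will be descriptive only"; removing it leaves 2 × 19 = 38. Any morbidity and no morbidity are complements, so they give the same interaction test twice. If only the 14 continuous or time-to-event rows of the supplement's section 5 table and any morbidity were fitted, there would be 2 × 15 = 30.
- Upward: the section 5 table marks 26 rows for modelling, giving 52. Splitting both grade outcomes into six grades adds 5 + 5 models: 36 models, 72 terms.

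**3. Chance findings, if the terms were tested.** No alpha is given. I assume two-sided 5%, matching the nominal 95% intervals. Under independence, P(at least one false positive) = 1 − 0.95^k:

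| k | Probability |
|---|---|
| 30 | 78.5% |
| 38 | 85.8% |
| 40 | 87.1% |
| 52 | 93.1% |
| 72 | 97.5% |

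The expected number at k = 40 is 40 × 0.05 = 2.0.

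Secondary outcomes in the same patients are correlated, so independence gives the high end. Simulation with equicorrelated normal statistics, k = 40:

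| Structure | Probability |
|---|---|
| Two independent blocks of 20, within-block correlation 0.3 | 79% |
| Same, 0.5 | 66% |
| Same, 0.7 | 49% |
| One common correlation of 0.5 | 57% |
| One common correlation of 0.8 | 28% |

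**4. Sparse binary outcomes.** The figures in step 3 give every test exact 5% size. Simulating an unadjusted Wald test of a logistic interaction with 18 patients per cell gives a true size of about 0.0% at a 5% event rate (87% of datasets not estimable), 0.2% at 10%, 2.7% at 20% and 4.6% at 30%. Many of the planned outcomes are binary, so the true probabilities would be below those in step 3.

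**5. Precision.** Assume 72 patients, 36 per arm, with the factor split evenly (18 per cell).
- Continuous outcome, in SD units: SE of the interaction = √(4/18) = 0.471. The interaction detectable with 80% power is (1.96 + 0.84) × 0.471 ≈ 1.32 SD, against (1.96 + 0.84) × √(2/36) ≈ 0.66 SD for a main effect.
- Binary outcome, assumed 30% event rate in every cell: variance = 4 × 0.30 × 0.70 / 18 = 0.0467, SE = 0.216, 95% half-width = 1.96 × 0.216 = 0.42, or ±42 percentage points.

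Uneven splits are worse: a 70/30 split needs about 1.44 SD.

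**The case against.** The strongest reply is that no test is planned. Section 15.3 only lifts a statement that p-values are not needed, and section 15.4 names no p-value, threshold or decision rule. The SAP's ban has no exception, and the supplement presents itself as filling in detail that SAP 3.7.2 deferred, so the ban can be read as governing. Section 15.3 also calls later subgroup analyses exploratory and informal, and SAP section 1 does not curtail exploratory work. Looking at effects by the two minimisation factors, declared in advance, is a common exploratory step.

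Most of this stands. A reader might infer that the supplement commits the trial to at least 40 significance tests, more likely than not to yield a false positive. The documents do not support that: tests are implied at most, 40 is not a floor, and the probability falls below one half under strong correlation and falls further with sparse outcomes. A reader might also infer that a chance interaction would steer the definitive trial. SAP 3.7.1 bases progression on recruitment, engagement, adherence, retention and safety, and nothing links these interactions to future eligibility or stratification.

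The reply does not remove the conflict. The exception would have no purpose if the ban simply applied, and the SAP delegates secondary-outcome detail to this supplement. The supplement also plans interaction analyses where the parent documents say there are none.

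**Conclusion.** The point holds as an unreconciled contradiction. Supplement 15.3 and 15.4 depart from protocol 11.2 and 11.7 and from SAP 4.1, 6.4 and 6.5, and leave open whether interaction p-values will appear.

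Its size is conditional on three things: that every planned model is fitted (about 40 terms, plausibly 30 to 70), that each term is tested, and that the level is two-sided 5%. For 40 terms the chance of at least one false positive then runs from 87% under independence to 28% at a common correlation of 0.8, before allowing for the conservatism of tests on sparse binary outcomes. That is well above a nominal 5% across the correlations tried, but no single figure should be quoted as the trial's error rate. With about 18 patients per cell, the interactions are in any case too imprecise to support a subgroup claim.

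**What to change.** Before database lock, amend the supplement in three places:

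1. **Section 15.3:** delete the opening clause that excepts the stratification factors, so that the descriptive, no-p-value rule of SAP 4.1 and protocol 11.7 covers these analyses too.
2. **Section 15.4:** relabel the two interaction bullets as exploratory effect-modification analyses not planned in the protocol or SAP. Report the effect in each stratum and the interaction estimate with a nominal 95% confidence interval and no p-value, and state that no subgroup claim will rest on them.
3. **Section 4.1:** state that taking the interaction term as the treatment effect applies only to treatment-by-time models, not to the stratification-factor interactions.

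The cost is a wording change, with no new data or patients. The one thing given up is p-values for interactions that the trial can barely estimate.

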#### 15.3.1 HADS (anxiety)

| #  | Outcome Measures                                          | Control | Intervention | Delta |
|----|-----------------------------------------------------------|---------|--------------|-------|
| 8b | xxii. HADS                                                |         |              |       |
|    | • Anxiety (is +ve change since baseline $\geq$ MCID, Y/N) | X*      | X*           | X†    |
|    | • Anxiety (is -ve change since baseline $\geq$ MCID, Y/N) | X*      | X*           | X†    |

† = difference between arms: ie compare the control change since baseline to the intervention change since baseline.

\* = this is a count and percentage of all the patients in that arm whose change since baseline exceeds the MCID.

- Anxiety (is +ve change since baseline  $\geq$  MCID, Y/N)
  - This is the proportion of participants with a positive change at the pre-op 3 assessment since baseline of at least 1.7 points as the minimum clinically important difference (Y/N). This is a binary variable.
- Anxiety (is -ve change since baseline  $\geq$  MCID, Y/N)
  - This is the proportion of participants with a negative change at the pre-op 3 assessment since baseline of at least 1.7 points as the minimum clinically important difference (Y/N). This is a binary variable.

The minimum clinically important difference for HADS is 1.7 points, see Lemay KR, et al [8]

### 15.3.2 HADS (depression)

| #  | Outcome Measures                                             | Control | Intervention | Delta |
|----|--------------------------------------------------------------|---------|--------------|-------|
| 8b | xxii. HADS                                                   |         |              |       |
|    | • Depression (is +ve change since baseline $\geq$ MCID, Y/N) | X*      | X*           | X†    |
|    | • Depression (is -ve change since baseline $\geq$ MCID, Y/N) | X*      | X*           | X†    |

† = difference between arms: ie compare the control change since baseline to the intervention change since baseline.

\* = this is a count and percentage of all the patients in that arm whose change since baseline exceeds the MCID.

As HADS (anxiety) above.

## 15.4 Sensitivity Analyses

Sensitivity analyses will be done on at least the following:

- **Per-protocol analysis.** The per-protocol analysis will repeat the above models using the per protocol population as defined in section 3.
- **Stratification factors.** The two stratification factors are performance status (“0” vs “1-2”) and age at diagnosis (“< 70 years” and “ $\geq$ 70 years”). For sensitivity analysis we will do the following:
  - Repeat the models with an interaction term between age at diagnosis (“< 70 years” and “ $\geq$ 70 years”) and treatment. This will be expanded to “...and treatment and time” if time is an input variable, see below.
  - Repeat the models with an interaction term between performance status (“0” vs “1-2”) and treatment. This will be expanded to “...and treatment and time” if time is an input variable, see below.
  - Models measuring the state at one timepoint (eg discharge) or the state change between two timepoints will not need a time variable. Models measuring the state at two or more timepoints (eg baseline vs admission vs 30-days post-op) will need a time variable. In such cases, the interaction above will include the time variable. The paper at [7] is an example of this.
- **Other.** Other sensitivity analyses may be conducted if deemed necessary by the Trial Statistician.

## 17. APPENDIX: SCORING RULES

Where available, scoring rules are given below. To reduce duplication, rules that are explicated in the tables above are not duplicated here.

### 17.1 EQ-5D-5L: HRQoL using Patient Reported Outcome Measure (PROMs) EQ-5D-5L

- Sources: <https://euroqol.org/wp-content/uploads/2021/01/EQ-5D-5LUserguide-08-0421.pdf>
- Online calculator: [https://euroqol.org/wp-content/uploads/2020/12/ENG\\_value-set\\_STATA.txt](https://euroqol.org/wp-content/uploads/2020/12/ENG_value-set_STATA.txt)

#### 17.1.1 Summary index value

Each variable has a tick box, where each dimension has five response levels: 1=no problems, 2=slight problems, 3=moderate problems, 4=severe problems, 5=unable to /extreme problems.

The answers are concatenated into a code (eg “12213”) and converted to a utility code, either manually or via code such as STATA. The scoring rules to translate the code into a utility code can be gotten from the user guide “EQ-5D-5L User Guide” at the EQ-5D website at <https://euroqol.org/wp-content/uploads/2021/01/EQ-5D-5LUserguide-08-0421.pdf>

Conversely, the scoring rules for translating the code to an utility code can be deduced by looking at the STATA code available [https://euroqol.org/wp-content/uploads/2020/12/ENG\\_value-set\\_STATA.txt](https://euroqol.org/wp-content/uploads/2020/12/ENG_value-set_STATA.txt). That dataset gives us this lookup table:

| variable | value | weight |
|----------|-------|--------|
| mobility | 1     | 0      |
| mobility | 2     | 0.058  |
| mobility | 3     | 0.076  |
| mobility | 4     | 0.207  |
| mobility | 5     | 0.274  |
| selfcare | 1     | 0      |
| selfcare | 2     | 0.05   |
| selfcare | 3     | 0.08   |
| selfcare | 4     | 0.164  |
| selfcare | 5     | 0.203  |
| activity | 1     | 0      |
| activity | 2     | 0.05   |
| activity | 3     | 0.063  |
| activity | 4     | 0.162  |
| activity | 5     | 0.184  |
| pain     | 1     | 0      |
| pain     | 2     | 0.063  |
| pain     | 3     | 0.084  |
| pain     | 4     | 0.276  |

|         |   |       |
|---------|---|-------|
| pain    | 5 | 0.335 |
| anxiety | 1 | 0     |
| anxiety | 2 | 0.078 |
| anxiety | 3 | 0.104 |
| anxiety | 4 | 0.285 |
| anxiety | 5 | 0.289 |

So a code of “12213” would translate as  $1 \times 0 + 2 \times 0.05 + 2 \times 0.05 + 1 \times 0 + 3 \times 0.104 = 0 + 0.1 + 0.1 + 0 + 0.312 = 0.512$

The EQ-5D-5L summary index value ranges from less than 0 (indicating a health state worse than death) to 1 (indicating full health). Higher scores represent better health states.

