### **11.11. Health Economic analysis**

Appropriate health economic evaluation will be conducted and will be detailed in a separate health economic analysis plan. Data on health economic aspects (intervention costs, healthcare resource use, and quality-adjusted life years) will be collected (see 9.6.3) and described to allow for planning of the health economics analysis in a future definitive trial.

Intervention costs will include training for intervention delivery, intervention delivery, administrative time, and meal replacement products.

Healthcare resource use will be quantified base on self-reported questions as per 9.6.3 and hospital records. The hospital records will be used to quantify secondary care resource use, as it is anticipated that all secondary care for each patient will be received at the recruitment hospital. Secondary care

resource use will include complications, fitness to discharge, operative outcomes, and oncological outcomes as per 9.6.3. Healthcare resource use will be valued using unit costs from UK NHS reference costs and the most recent Personal Social Services Research Unit.

Quality-adjusted life years will be estimated based on the collected EQ-5D-5L data using UK utility values.

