### 12.1 xxi. EQ-5D-5L

This secondary outcome is displayed by timepoint. The information to calculate it is derived from the CRF EQ-5D-5L. It is in two parts: a summary index value derived from the code, and a visual analogue scale score (VAS). Instructions for calculating these values are given in the appendices.

- The EQ-5D-5L summary index value ranges from less than 0 (indicating a health state worse than death) to 1 (indicating full health). Higher scores represent better health states.
- The EQ-5D-5L Visual Analogue Scale (VAS) ranges from 0 to 100. The maximum value is 100 and represents the best health you can imagine. The minimum value is 0 and represented the worst health you can imagine.

We will treat both variables as scores and continuous variables. The scoring rules are in the appendices.

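### The printed EQ-5D-5L scoring rule in the SAP supplement gives full health a score of 0 and the worst state 6.425, contradicting the supplement's own range and direction for the index

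*Combined protocol and SAP*

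**What the plan says.** Supplement section 12.1 makes the EQ-5D-5L summary index one of two EQ-5D-5L scores to be treated as continuous, and sends the reader to the appendices for scoring. It defines the scale: "The EQ-5D-5L summary index value ranges from less than 0 (indicating a health state worse than death) to 1 (indicating full health"). Section 17.1.1 repeats that range and adds "Higher scores represent better health states".

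Section 17.1.1 describes the conversion in outline: "The answers are concatenated into a code (eg “12213”) and converted to a utility code". It allows this to be done by hand or by software, and cites an external user guide and a Stata value-set file as sources of the scoring rules. It then prints a table of weights taken from that file, with a separate weight for each of the five levels of each of the five dimensions, and works one example, 12213. Each weight is multiplied by its level number and the products are added: "0 + 0.1 + 0.1 + 0 + 0.312 = 0.512".

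Supplement sections 4.2 and 5 place the index among the outcomes to be modelled, at baseline, pre-operative assessment 3 and 30 days after surgery. Protocol section 11.11 says "Quality-adjusted life years will be estimated based on the collected EQ-5D-5L data using UK utility values". SAP section 6.8 and supplement section 13 leave health economics to a separate plan.

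**The concern.** The weights are 0 at level 1 (no problems) and rise with severity in every dimension. They behave as losses of health, already specific to the level reported. The worked example treats them as something else. It scales each one by the level number, which counts severity twice, and reports the total itself as the index. A total of losses is low for healthy people and high for ill people, the opposite of the direction stated just below the example.

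At stake is the between-group comparison of the EQ-5D-5L index. Under the printed rule, a deterioration in one arm would usually appear as an improvement. The example does not expose itself, because 0.512 looks like an ordinary utility value. The planned independent repeat analysis would not necessarily catch it either: SAP section 7 is directed at the primary outcomes, and its Table 4 lists only the recruitment, engagement, adherence and retention variables. Supplement section 17.3 notes that HADS is generated within REDCap. No such statement is made for EQ-5D-5L.

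**Working it through.** **Inputs** (all from supplement section 17.1.1), weights by level 1 to 5:

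| Dimension | 1 | 2 | 3 | 4 | 5 |
|---|---|---|---|---|---|
| Mobility | 0 | 0.058 | 0.076 | 0.207 | 0.274 |
| Self-care | 0 | 0.050 | 0.080 | 0.164 | 0.203 |
| Activity | 0 | 0.050 | 0.063 | 0.162 | 0.184 |
| Pain | 0 | 0.063 | 0.084 | 0.276 | 0.335 |
| Anxiety | 0 | 0.078 | 0.104 | 0.285 | 0.289 |
| Sum | 0 | 0.299 | 0.407 | 1.094 | 1.285 |

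**Step 1: reproduce the printed figure.** Rule A, as printed, is the sum of (level × weight). For 12213: 1×0 + 2×0.05 + 2×0.05 + 1×0 + 3×0.104 = 0.512. The figure reproduces exactly, so the fault lies in the rule and not in the addition. The alternatives give other values: the plain sum of weights is 0.204, 1 minus that sum is 0.796, and 1 minus the sum of (level × weight) is 0.488.

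**Step 2: compare with a rule that has the stated properties.** Rule B is 1 minus the sum of the five level weights, each used once.

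| State | Rule A (printed) | Rule B |
|---|---|---|
| 11111 | 0 | 1.000 |
| 12213 | 0.512 | 1 − 0.204 = 0.796 |
| 22222 | 2 × 0.299 = 0.598 | 1 − 0.299 = 0.701 |
| 33333 | 3 × 0.407 = 1.221 | 1 − 0.407 = 0.593 |
| 44444 | 4 × 1.094 = 4.376 | 1 − 1.094 = −0.094 |
| 55555 | 5 × 1.285 = 6.425 | 1 − 1.285 = −0.285 |

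**Step 3: all 5⁵ = 3,125 states.**
- Rule A runs from 0 to 6.425. No state is below 0, and 2,848 states (2,848/3,125 = 91%) exceed 1.
- Rule B runs from −0.285 to 1, with 159 states below 0. This agrees with the stated range and direction.

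**Step 4: direction.** Both level and weight increase down every scale, so level × weight increases too. Under Rule A, a state that worsens on any dimension without improving on another therefore always scores higher.

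Where two states trade one dimension against another, the order need not reverse. For example, 11141 scores 4×0.276 = 1.104 under Rule A and 1 − 0.276 = 0.724 under Rule B. State 51111 scores 5×0.274 = 1.370 and 1 − 0.274 = 0.726. Both rules put 51111 higher. Among all pairs of states that differ under both rules, 5.75% keep the same order. The correlation between the two rules across all states is −0.98.

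**The case against.** The strongest reply is that the worked line is an illustration and not the only authority. Section 17.1.1 points to a user guide and to Stata code, and an analyst who runs that code need never apply the printed rule. This stands. The documents show a wrong written rule. They do not show that any value has been or will be computed wrongly. It does not remove the defect, because manual conversion is expressly allowed and the only calculation set out in full contradicts the definition of the index.

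Second, the supplement nowhere states the formula 1 minus the sum of weights, so 0.796 and −0.285 are derived values. The stated range and direction alone would also fit 1 minus the sum of (level × weight), which runs from −5.425 to 1. What tells against that version is the table itself: the weights already differ by level, so multiplying by level has no role. The cited code was not available for this check, so the formula should be confirmed against it.

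Third, two stronger readings are tempting and should be resisted. A reader might infer that every between-group difference would reverse. The 5.75% of state pairs that keep their order show that this is not so. A reader might also infer that the QALYs are wrong. Protocol section 11.11 refers to UK utility values under a separate health economic plan, and nothing in the documents says that plan adopts this worked example.

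Fourth, this is a secondary outcome in a feasibility trial that reports no P-values and treats its intervals as descriptive. That limits the consequence but does not make the rule usable.

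**Conclusion.** Wrong as written. The printed rule contradicts the stated range and direction of the index in the same section and in section 12.1. It scores full health 0 instead of 1 and the worst state 6.425 instead of a value below 0, and it puts 91% of states above the stated maximum.

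The effect on results is conditional. If the printed rule is followed, the modelled index is on a meaningless scale and between-group differences will generally, not always, change sign. If the cited code is used and is consistent with the stated range and direction, the reported values will not carry the error, but the pre-specified rule and the analysis will disagree. The EQ-5D visual analogue scale is scored separately and is untouched. No progression criterion uses the index.

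The contradiction itself rests only on the printed table and the stated range and direction. The replacement values also rest on reading each weight as a loss taken once and subtracted from 1, which the level-specific table strongly supports.

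**What to change.** In supplement section 17.1.1, replace the rule and the example with:

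index = 1 − (sum of the five level-specific weights, each used once)

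For 12213: 1 − (0 + 0.050 + 0.050 + 0 + 0.104) = 0.796.

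Before issue, confirm the formula and this value against the cited value-set code. Name one scoring source as definitive, so that manual and coded routes cannot diverge. Add two checks to the analysis program: 11111 must return 1.000 and 55555 must return −0.285 (both derived from the printed table). Ask the authors of the health economic plan to confirm that it does not use the printed example.

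The cost is one corrected line, one sentence naming the source and two checks in the code. No change to data collection, sample size or the progression criteria is needed.
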